## Abstract

**Background:**

For esophageal cancer patients, radical esophagolymphadenectomy is the cornerstone of multimodality treatment with curative intent. Transthoracic esophagectomy is the preferred surgical approach worldwide allowing for *en-bloc* resection of the tumor with the surrounding lymph nodes. However, the percentage of cardiopulmonary complications associated with the transthoracic approach is high (50 to 70%).

Recent studies have shown that robot-assisted minimally invasive thoraco-laparoscopic esophagectomy (RATE) is at least equivalent to the open transthoracic approach for esophageal cancer in terms of short-term oncological outcomes. RATE was accompanied with reduced blood loss, shorter ICU stay and improved lymph node retrieval compared with open esophagectomy, and the pulmonary complication rate, hospital stay and perioperative mortality were comparable. The objective is to evaluate the efficacy, risks, quality of life and cost-effectiveness of RATE as an alternative to open transthoracic esophagectomy for treatment of esophageal cancer.

**Methods/design:**

This is an investigator-initiated and investigator-driven monocenter randomized controlled parallel-group, superiority trial. All adult patients (age ≥18 and ≤80 years) with histologically proven, surgically resectable (cT1-4a, N0-3, M0) esophageal carcinoma of the intrathoracic esophagus and with European Clinical Oncology Group performance status 0, 1 or 2 will be assessed for eligibility and included after obtaining informed consent. Patients (*n* = 112) with resectable esophageal cancer are randomized in the outpatient department to either RATE (*n* = 56) or open three-stage transthoracic esophageal resection (*n* = 56). The primary outcome of this study is the percentage of overall complications (grade 2 and higher) as stated by the modified Clavien–Dindo classification of surgical complications.

**Discussion:**

This is the first randomized controlled trial designed to compare RATE with open transthoracic esophagectomy as surgical treatment for resectable esophageal cancer. If our hypothesis is proven correct, RATE will result in a lower percentage of postoperative complications, lower blood loss, and shorter hospital stay, but with at least similar oncologic outcomes and better postoperative quality of life compared with open transthoracic esophagectomy. The study started in January 2012. Follow-up will be 5 years. Short-term results will be analyzed and published after discharge of the last randomized patient.

**Trial registration:**

Dutch trial register: NTR3291 ClinicalTrial.gov: NCT01544790

## Background

In 2008 an estimated 482,300 people were diagnosed with esophageal cancer, and 406,800 patients died of the disease worldwide [1]. Radical esophagolymphadenectomy is the cornerstone of the multimodality treatment with curative intent [2-5].

Transthoracic esophagectomy is the preferred surgical approach worldwide allowing for *en-bloc* resection of the tumor with the surrounding para-tracheal, subcarinal and para-esophageal lymph nodes [6,7]. However, the percentage of cardiopulmonary complications associated with the transthoracic approach is high (50 to 70%) [6].

Minimally invasive esophagectomy was designed to reduce surgical trauma, resulting in lower morbidity and mortality rates. With regard to minimally invasive esophagectomy, review of the literature shows a substantial decrease in blood loss, postoperative complications and days of hospital stay, with comparable oncologic results [8-12].

In 2003 the robot-assisted thoraco-laparoscopic approach was developed at the University Medical Center Utrecht (UMCU), the Netherlands [13]. Robot-assisted thoraco-laparoscopic esophagectomy facilitates complex minimally invasive procedures with an enlarged, three-dimensional field of view. The articulated instruments allow dissection with seven degrees of freedom [13,14].

Until now there have been no prospective randomized controlled trials comparing robot-assisted minimally invasive esophagectomy with conventional open transthoracic esophagectomy. We present the protocol of the first randomized controlled trial comparing these two surgical approaches.

### Aim of the study

This is a randomized controlled parallel-group, superiority trial of robot-assisted thoraco-laparoscopic esophagectomy versus open three-stage transthoracic esophagectomy in patients with resectable intrathoracic esophageal cancer.

## Methods

### Objectives

Patients with resectable esophageal cancer are randomized at the outpatient department to either robot-assisted thoraco-laparoscopic esophagectomy or open three-stage transthoracic esophageal resection. The objective is to evaluate the efficacy, risks and cost-effectiveness of robot-assisted thoraco-laparoscopic esophagectomy as an alternative to open transthoracic esophagectomy as treatment for esophageal cancer. We hypothesize that robot-assisted minimally invasive thoraco-laparoscopic esophagectomy leads to a lower postoperative complication rate, less blood loss and a shorter hospital stay, with similar oncologic outcomes and better postoperative quality of life, compared with the open transthoracic esophagectomy (current reference standard of care).

### Study design

This is an investigator-initiated and investigator-driven randomized controlled parallel-group, superiority trial comparing robot-assisted thoraco-laparoscopic esophagectomy with traditional open three-stage transthoracic esophageal resection.

This study is conducted in accordance with the principles of the Declaration of Helsinki [15] and Good Clinical Practice Guidelines [16]. The independent ethics committee of the UMCU has approved the study. Written informed consent will be obtained from all participating patients. Clinical trial monitoring will be conducted by an independent data monitor (Julius Clinical Research, Zeist, the Netherlands).

### Study population

All adult patients (age ≥18 and ≤80 years) with histologically proven, surgically resectable (cT1-4a, N0-3, M0) squamous cell carcinoma, adenocarcinoma or undifferentiated esophageal carcinoma of the intrathoracic esophagus will be assessed for eligibility. Patients should have a performance status 0, 1 or 2 according to the European Clinical Oncology Group.

The Patients’ inclusion and exclusion criteria are:

Inclusion criteria

•Histologically proven squamous cell carcinoma, adenocarcinoma or undifferentiated carcinoma of the intrathoracic esophagus (including Siewert I and II).

•Surgically resectable (T1-4a, N0-3, M0).

•Age ≥18 and ≤80 years.

•European Clinical Oncology Group performance status 0,1 or 2.

•Written informed consent.

Exclusion criteria

•Carcinoma of the cervical esophagus.

•Carcinoma of the gastro-esophageal junction with the main part of the tumor in the gastric cardia (Siewert type III).

•Prior thoracic surgery at the right hemithorax or thoracic trauma.

### Study protocol

Patients are informed about the trial by one of our surgeons ([name] or [name]) at the outpatient department. After receiving the information, all patients have 1 week to consider their consent. After 1 week, patients are contacted by the coordinating researcher ([name]) to make an appointment to obtain and register informed consent.

After obtaining informed consent, randomization is done by computer-generated random numbers. Concealment of allocation is maintained by using sealed opaque envelopes. There is no blinding for the patient, surgeon and coordinating researcher because this is difficult in daily practice. However, the independent data monitoring safety committee is blinded to the allocated intervention. Within 1 week, patients will be informed about the allocated treatment. This study is completed funded by the Department of Surgery, UMCU. Multiple esophageal cancer biopsies for pathological analysis will be obtained through esophagogastroscopy, of which four biopsies will be snap frozen and stored for translational research. The physical status of the patient is assessed and preoperative testing is guided by institutional guidelines [17].

Neoadjuvant (radio)chemotherapy will be administered according to the current policy in the Netherlands and the UMCU [17]. Two additional blood samples will be obtained for translational research (proteomics) at the following times: before start of neoadjuvant treatment, the day of operation, after adjuvant treatment and with suspicion of recurrent disease.

After finishing preoperative neoadjuvant treatment, patients will be evaluated with a second computed tomography scan for metastases and resectability. When the tumor is considered to be resectable, patients will undergo the randomized intervention – either robot-assisted thoraco-laparoscopic esophagectomy or open three-stage transthoracic esophagectomy depending on randomization.

All resection specimens will be preserved and stored (biobank, tissue-microarray) for translational research.

The study started on 1 January 2012. Inclusion will take approximately 3 years. Follow-up for each patient will be 5 years. The total duration of the study will be 8 years.

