### Interim analysis

There will be one interim analysis. The stopping rule used for efficacy (that is, better outcome for the minimally invasive method as the primary endpoint) is the Peto approach, meaning *P* <0.001. The trial will not be stopped for futility (that is, no difference) as the robot-assisted minimally-invasive approach is being used by a growing numbers of centers worldwide and the outcome of all endpoints of this first randomized trial on this subject are relevant to healthcare professionals involved with this procedure in those hospitals. As is advised by the Dutch Central Committee on Research involving Human Subjects (CCMO), there is no formal stopping rule for harm.

After every 25 patients, individualized patient description charts including safety parameters will be presented to the Data Safety Monitoring Committee (DSMC). The DSMC will discuss these in a plenary or telephone conference with the study coordinator and principal investigator present. If the suspects are harmed (that is, worse outcome for the minimally invasive method) the DSMC will inform the trial research group. The trial research group will discuss in a plenary session together with the DSMC the potential harm per patient and will determine whether a relationship can be drawn between the minimally-invasive procedure and the adverse events. Consensus will be reached and the Medisch Ethische Toetsingscommissie will be informed.

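### The safety committee is blinded to allocation yet must act on a worse outcome in the robot arm, so it cannot detect a comparative excess of common complications as the plan is written

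*Protocol article*

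**What the plan says.** Under Study protocol, the article describes who knows the allocation. For the clinical side: "There is no blinding for the patient, surgeon and coordinating researcher because this is difficult in daily practice". For the committee: "the independent data monitoring safety committee is blinded to the allocated intervention".

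Under Interim analysis, the committee's material is a set of charts on individual patients, including safety parameters, delivered after every 25 patients. No grouping by arm, coded or open, is mentioned. On attendance: "The DSMC will discuss these in a plenary or telephone conference with the study coordinator and principal investigator present". On the trigger for action: "If the suspects are harmed (that is, worse outcome for the minimally invasive method) the DSMC will inform the trial research group". That group and the committee then meet in plenary, consider the potential harm patient by patient, and "will determine whether a relationship can be drawn between the minimally-invasive procedure and the adverse events". They reach consensus and the ethics committee is informed. The same section says, citing advice from the national committee on human-subjects research, that "there is no formal stopping rule for harm".

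**The concern.** The trigger is a comparison between arms. The body that must pull it is said not to know the arms, and the article gives no route by which it could learn them. With no formal harm rule, this review is the main trial-level protection described against the robot procedure doing worse.

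The second strand is independence. The committee discusses the charts in front of the study coordinator and principal investigator, and the judgement on causality is shared with the trial group. The trial is run at one centre. The same surgeons perform all procedures, their department funds the study, and the centre developed the technique. In that setting a judgement that the robot procedure is causing harm should be formed first by people outside the team.

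At stake is delayed recognition of an excess of complications in the robot arm. The primary test, sample size and type I error are not affected.

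**Working it through.** **Inputs.** From Sample size calculation: complication rates (MCDC grade 2 and higher) of 91% open and 69% robot; two-sided alpha 0.05; power 0.80; 51 per arm before dropout. From Interim analysis: charts after every 25 patients, so reviews at 25, 50, 75 and 100 of the 112 patients.

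**Check that the rates are read correctly.** With mean rate (0.91 + 0.69)/2 = 0.80,

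n per arm = [1.960 × √(2 × 0.80 × 0.20) + 0.842 × √(0.91 × 0.09 + 0.69 × 0.31)]² / 0.22²
= [1.109 + 0.458]² / 0.0484 ≈ 50.7, rounded up to 51.

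This matches the plan's 51 per arm (102 in total).

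**What a committee without arm information sees.** With 1:1 allocation the pooled rate is (robot rate + open rate)/2.

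- Robot better by 22 points (69% v 91%): (0.69 + 0.91)/2 = 0.80.
- Robot worse by 22 points (91% v 69%): (0.91 + 0.69)/2 = 0.80.
- No difference at 80% v 80%: 0.80.

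In each case a batch of 25 is expected to contain 25 × 0.80 = 20 patients with an event. If instead the open rate stayed at 91% and the robot rate rose above it, the pooled rate would move, to at most (0.91 + 1.00)/2 = 0.955. It would still not show which arm had moved it. Pooled data carry no information on direction.

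**What single charts add.** When about 20 of 25 patients have an event of this kind, the charts show that complications happen. They do not show that one arm has more of them.

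**What a table by arm would add.** Suppose the observed difference is 22 points (91% v 69%) with an equal split. The approximate 95% half-width is 1.96 × √[(0.91 × 0.09 + 0.69 × 0.31)/m] = 1.96 × √(0.2958/m), with m patients per arm.

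| Patients reviewed | m per arm | Half-width (points) | Approximate 95% interval (points) |
|---|---|---|---|
| 25 | 12.5 | 30 | −8 to 52 |
| 50 | 25 | 21 | 1 to 43 |
| 75 | 37.5 | 17 | 5 to 39 |
| 100 | 50 | 15 | 7 to 37 |

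The table says little at the first review and becomes informative as data accumulate, so it should be cumulative and not restricted to the latest batch.

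**The case against.** Several points on the other side have force.

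- **Blinded need not mean pooled.** A committee shown groups A and B is still blinded and can see that one is doing worse. The article neither describes nor excludes this. It follows that deleting the blinding statement is not the only remedy: coded review, with the key available on request, would also reconcile the sections. But naming the minimally invasive method as the worse one still needs the key, and the text gives the committee no access to it.
- **The review is not useless.** A reader might infer that the whole harm safeguard fails. The text does not support that. A blinded committee can flag a death or another striking event, and attribution to an arm can follow in the joint session. Charts may also contain events rarer than grade 2 complications. What fails is the comparative trigger. The route that remains leaves attribution to a discussion shared with the investigators.
- **The efficacy rule.** A reader might infer that the blinding also blocks the interim P <0.001 boundary. Interim analysis does not say who runs or sees that test, so no such conclusion can be drawn.
- **Exposure of investigators to emerging data.** This adds little. The same surgeons do every operation, and surgeons and the coordinating researcher already know arms and outcomes. The loss of independent deliberation matters more.
- **An article leaves charter detail elsewhere.** True, so the absence of a charter or a described closed session is not the point. The conflict lies between two statements that the article does make.
- **Other oversight exists.** An independent data monitor is in place and the ethics committee is informed, but neither is described as comparing arms. The absence of a formal harm rule follows outside advice and is not criticised here.

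**Conclusion.** The point holds in a limited form. Read literally, Study protocol and Interim analysis cannot both be followed: a committee blinded to allocation and given individual charts cannot recognise a worse outcome in the robot arm when the events are common in both arms. At the design rates it would see 80% pooled, about 20 of 25 patients per batch, whether the robot procedure were 22 points better or 22 points worse. Its deliberation, as described, also takes place with investigators present and ends in consensus with the trial group.

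This rests on four assumptions: 1:1 allocation; grade 2 and higher complications as the example, since the article does not list the safety parameters in the charts; charts that do not reveal the operation (if they did, the blinding statement would be untrue); and the study coordinator being the unblinded coordinating researcher of Study protocol. The principal investigator's blinding status is not stated outright, although surgeons are unblinded. The conflict over the trigger does not depend on that last assumption.

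**What to change.** Reconcile the two sections:

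1. After every 25 patients, give the committee a cumulative safety table by coded arm (A/B), for example deaths, reoperations, and grade 2 and higher and grade 3 and higher complications, with confidence intervals. Someone outside the operating team should prepare it. The key should be held by the committee or be available to it on request.
2. Reword the blinding statement in Study protocol to say exactly this.
3. Limit the study coordinator and principal investigator to an open part of the meeting.
4. Have the committee form its own recommendation before any joint discussion with the trial group.

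No formal harm boundary is needed, so the change is compatible with the advice that the article cites. The cost is some rewording, one table per review from data already collected at reviews already scheduled, and some loss of committee blinding.

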### Surgery

All procedures (robot-assisted thoraco-laparoscopic esophagectomy or open transthoracic esophagectomy) will be carried out by the same experienced surgeons in the UMCU ([name] and [name]). All patients will receive an epidural catheter to provide adequate postoperative analgesia. Patients will be intubated with a left-sided double-lumen tube to enable selective desufflation of the right lung during the thoracic phase in both procedures.

Prophylactic antibiotics cefazolin (2,000 mg) and metronidazole (500 mg) will be administered 30 minutes prior to incision [14]. An intravenous injection of 10 mg/kg methylprednisolone will be administered 30 minutes prior to incision to minimize postoperative pulmonary complications [18]. During single-lung ventilation, a pressure-controlled ventilation strategy will be used with a maximum pressure of 20 cm H_2_O [19].

### Open three-stage transthoracic esophagectomy

The patient is placed in a left lateral decubitus position and the procedure commences with a right posterolateral thoracotomy. After incision and desufflation of the right lung, the pulmonary ligament is incised followed by identification of the azygos vein. The azygos vein is clipped and ligated at the level of the azygos arch. The thoracic duct is identified, clipped and ligated. The esophagus is resected *en bloc* with the surrounding mediastinal lymph nodes. The resected specimen will contain right-sided paratracheal (lymph node station 2R), tracheobronchial (lymph node station 4), aortopulmonary window (station 5), carinal (station 7) and peri-esophageal (station 8) lymph nodes [20].

Chest tubes are placed and the thoracotomy wound is closed using intracutaneous closure with absorbable sutures.

The patient is turned to a supine position for the abdominal phase via supra-umbilical laparotomy. The stomach is mobilized with special care for the gastroepiploic and short gastric vessels. The left gastric artery is identified, clipped and ligated. Lymph node dissection is performed around the celiac trunk and the lesser omentum. A linear stapler (GIATM 80, 3.8 mm; Covidien, Mansfield, MA, USA) is used to create a gastric conduit 4 cm wide, which is routinely oversewn [21]. The gastric conduit is pulled up through the mediastinum along the original anatomic tract of the esophagus with the aid of a plastic tube (laparoscopic camera bag). A cervical handsewn end-to-side anastomosis is created between the gastric tube and the cervical esophagus using a 3/0 polydioxanone single-layer running suture. A feeding jejunostomy is placed in the second loop after the ligament of Treitz for postoperative feeding. The abdomen is closed in layers with PDS loop for the fascia and skin intracutaneously with monocryl. Patients are transferred to the ICU after the surgical procedure.

### Robot-assisted minimally invasive thoraco-laparoscopic esophagectomy

Robot-assisted minimally invasive thoraco-laparoscopic esophagectomy was described previously [14]. For the thoracic phase, the patient is positioned in the left lateral decubitus position, tilted 45° towards the prone position. The robotic system (daVinci Si; Intuitive Surgical Inc., Sunnyvale, CA, USA) is brought into the field at the dorsocranial side of the patient. Three ports are placed for the robotic system as well as two thoracoscopic ports for the assisting surgeon (Figure 1a). After incision and installation of the operation robot and selective desufflation of the right lung, the pulmonary ligament is divided. Hereafter, the parietal pleura is dissected at the anterior side of the esophagus from the diaphragm up to the azygos arch. The azygos vein is ligated with Hem-o-lok (Teleflex Medical, Weck Drive, NC, USA) and divided [22]. Dissection of the parietal pleura is continued above the azygos arch to establish dissection of the right paratracheal lymph nodes. At the posterior side of the esophagus, the parietal pleura is dissected cranially to caudally along the azygos vein, including the thoracic duct. The thoracic duct is clipped with a 10 mm endoscopic clipping device (Endoclip™ II; Covidien) to prevent chylous leakage. To facilitate esophageal mobilization a penrose drain is placed around the esophagus to manipulate the esophagus for further mobilization. The esophagus is resected *en bloc* with the surrounding mediastinal lymph nodes. The resection specimen will contain the same lymph nodes as described for the open procedure.

**Figure 1 F1:**
[figure not shown]
**Trocar arrangement during the robot****assisted thoracoscopic phase.** (**a**) Trocar arrangement during robot-assisted thoracoscopic phase. La, left robotic arm (fourth intercostal space); a, assistant thoracoscopic working port (fifth and seventh intercostal space); ca, robotic camera arm (sixth intercostal space); ra, right robotic arm (eighth intercostal space) [14]. (**b**) Trocar arrangement during the laparoscopic abdominal phase. The camera was inserted through the 10 mm para-umbilical trocar port and two 5 mm trocars were used as laparoscopic working ports. The liver retractor was inserted through the 12 mm right para-rectal trocar port. The harmonic scalpel was inserted through the 12 mm paraumbilical port [14]
.

For the abdominal phase, the patient is placed in a supine position. Figure 1b shows the position of the laparoscopic trocars. The lesser omentum is opened and transected closely to the liver, until the left crus of the diaphragm is reached. Hereafter, the greater gastric curvature is dissected using a harmonic ace. An abdominal lymphadenectomy is performed including lymph nodes surrounding the celiac trunk, along the left gastric and splenic artery and the lesser omental lymph nodes. The left gastric artery and vein are ligated with Hem-o-lok (Teleflex Medical) and transected at their origin.

Through a left-sided vertical incision along the sternocleidomastoid muscle, the cervical phase of esophagectomy is initiated to facilitate mobilization of the cervical esophagus. No formal cervical lymph node dissection is carried out, but macroscopically suspected cervical lymph nodes are dissected. The cervical esophagus is transected and a cord is attached to the specimen. The dissected esophagus *en bloc* with the surrounding lymph nodes are pulled down through the mediastinum under laparoscopic view.

Hereafter, the left para-umbilical trocar port is widened to a 5 to 7 cm transverse transabdominal incision. The resection specimen is removed through this incision with a wound drape (3M) to create the gastric conduit extracorporally. A linear stapler (GIATM 80, 3.8 mm; Covidien) is used to create a gastric conduit 4 cm wide, which is routinely oversewn [21]. The gastric conduit is pulled up through the mediastinum along the original anatomic tract of the esophagus with the aid of a plastic tube (laparoscopic camera bag). A cervical handsewn end-to-side anastomosis is created between the gastric tube and the cervical esophagus using a 3/0 polydioxanone single-layer running suture. A feeding jejunostomy is placed in the second loop after the ligament of Treitz for postoperative feeding. The abdomen is closed in layers with PDS loop for the fascia and skin intracutaneously with monocryl. Patients are transferred to the ICU after the surgical procedure.

